### Intervention

The participants in the treatment condition will receive eight individual face-to-face sessions of PCT, a therapy based on the cognitive model of Beck [84], developed specifically to prevent relapse in remitted MDD patients. The main elements of PCT are (i) identifying and challenging dysfunctional attitudes, (ii) internalising more helpful attitudes, (iii) enhancing the formation of specific memories of positive events, and (iv) formulating future relapse prevention strategies [6, 85].

PCT is provided by experienced and accredited psychologists, fully trained in cognitive behavioural therapy, who have received an additional two-day training in delivering PCT in the context of this study (by [name] and [name]). To establish an adequate level of treatment integrity, therapists will strictly follow a treatment manual [85] and will be supervised by a cognitive behavioural therapy supervisor ([name]). Finally, the treatment sessions will be audio-recorded to allow reviewing by the supervisor and researchers (only when participants give their permission).

### Measures

#### Primary outcome measures

The primary outcome of the cross-sectional assessment of rrMDD characteristics is threefold: it concerns baseline characteristics at T0 in (i) cognitive biases to negative and positive emotional information (measured with the Attentional Response to Distal vs. Proximal Emotional Information task (ARDPEI) [86], an adapted version of the Emotional Reasoning Task [87] and an Implicit Association Task (IAT) [88]); in (ii) blood oxygenation level dependent (BOLD) response (during an Emotion Regulation Task (ERT) (similar as in [81, 89]), a Verbal Working Memory Task (VWMT) [90], and during resting state; and in (iii) the PDR during these neurocognitive tasks.

Changes in these measures following PCT at T1 are the main study parameters in the assessment of the working mechanisms of PCT. The primary outcome for the assessment of treatment predictors concerns (i) depressive symptomatology, as measured with the Inventory of Depressive Symptomatology self-report version (IDS –SR30) [91] at T0, T1 and T2, and (ii) time to relapse and number of relapse over the course of the study, as measured with the Structured Clinical Interview for DSM-IV disorders (SCID-I) [92] at T1 and T2, in combination with the life chart method at T2.

#### Secondary outcome measures

Secondary parameters concern the following measures at T0 and changes therein following therapy (at T1), as these measurements provide additional information to interpret and understand the changes in neurocognitive functioning: Positive and Negative Affect Scale (PANAS) [93], Domains and Dimensions of Pleasure Scale (DDOPS) [94], Leuven Adaptation of the Rumination on Sadness Scale (LARSS) [95], Emotion Regulation Questionnaire (ERQ) [96], Responses on Positive Affect questionnaire (RPA) [97], Dysfunctional Attitude Scale form A (DAS-A) [98], NEO Five Factor Inventory (NEO-FFI) [99], Leiden Index of Depression Sensitivity–2nd revision (LEIDS-RR) [100], Bermond-Vorst Alexithymia Questionnaire (BVAQ) [101], and Wechsler Adult Intelligence Scale-IV (WAIS-IV) subtests (digit-span, letter-number sequencing, and digit-symbol substitution) [102].

Other study parameters that will be measured during MRI concern skin conductance reactivity (SCR), heart rate variability (HRV), and respiration cycle (RC), in order to provide additional measures of physiological arousal that can explain part of the fMRI and PDR signal and in order to remove physiological noise from the functional MRI data.

Finally, assessment of childhood trauma (using the Childhood Trauma Questionnaire, short form (CTQ-SF)) [103] is performed at T0 to assess moderating effects on treatment success. At T1, the Helping Alliance Questionnaire-II (HAQ-II) [104] will be administered in the PCT condition to assess the role of therapeutic relationship in therapy success. At T1 and T2, the Brugha recent life events questionnaire [105] will be administered to obtain information on the occurrence of life events during the trial. All questionnaires have been validated and have shown good reliability. An overview of the assessments used per treatment phase is provided in Table 1.

**Table 1 Tab1:** Overview of assessments

	Screening	Baseline T0	Follow-up T1 (3 month)	Follow-up T2 (18 month)
IDS-SR	x	x	x	x
SCID-I interview			x	
incl. Life chart method	x			x
DART	x			
ERQ		x	x	
LEIDS-RR		x	x	
LARSS		x	x	
RPA		x	x	
BVAQ		x	x	
CTQ		x		
NEO-FFI		x	x	
DAS		x	x	x
PANAS		x	x	
DDOPS		x	x	
ARDPEI with PDR		x	x	
IAT with PDR		x	x	
Emotional Reasoning Task		x	x	
WAIS-IV subtests		x	x	
fMRI ERT with PDR + SCR + HRV + RC		x	x	
fMRI VWMT with PDR + SCR + HRV + RC		x	x	
fMRI Resting State with SCR + HRV + RC		x	x	
MRI T1 with SCR + HRV + RC		x	x	
MRI arterial spin labelling with HRV + RC		x	x	
HAQ-II			x	
Brugha list			x	x

### Procedure

#### Overall procedure

All data will be collected at the University Medical Center Groningen, the Netherlands. Individuals interested in participation will contact the researchers on their own initiative, following public advertisement. During the screening, the researchers will first check if the participant fully understands the study, before the participant will sign an informed consent form. Then the SCID-I, IDS-SR, Dutch Adult Reading Test (DART) [106], an MRI checklist and a questionnaire with several socio-demographic background questions will be administered, all to confirm that the participant meets the inclusion criteria.

To minimize the burden on the day of scanning, a number of questionnaires will be sent to the participants 1 week prior to the baseline assessment. During baseline assessment the rest of the self-report questionnaires will be administered, the cognitive tests will be performed (ARDPEI and IAT, during which pupil dilation and gaze tracking will be measured with the Research Eyelink 1000 Eye tracker (Mississauga, Canada), plus the Emotional Reasoning Task and the WAIS-IV subtests), and finally participants will engage in an MRI-scanning session.

After baseline assessment, HC participants have finished their participation, and participants in the rrMDD group undergo either eight sessions of PCT, or are in the waiting list condition. Shortly after treatment (3 months following baseline), the first follow-up assessment T1 will be performed, in which the whole baseline procedure will be repeated (minus the CTQ and plus the HAQ-II and Brugha list). Eighteen months after baseline, a shortened version of the clinical assessment (SCID-I (including assessment of psychopathology since T0 with the life chart method), IDS-30 and DAS) will be repeated to assess stability of clinical state. Participants will receive 25 euro per assessment, 75 euro in total, plus reimbursement of travel expenses.

#### MRI procedure

MRI scanning will be performed on two scanners (due to an unforeseen scanner replacement). The 25 HC and the first 50 rrMDD subjects will be scanned on a Philips Intera 3 Tesla MR system, equipped with a 32-channel receiver head coil, at the NeuroImaging Center, University Medical Center Groningen. The last 25 rrMDD patients (all in the treatment condition) will be scanned on a Siemens 3 Tesla Magneton Prisma MR system (equipped with a 64-channel receiver head coil), at the Radiology Department of the University Medical Center Groningen, using imaging protocols harmonized to the Philips protocols.

The scanning procedure involves two functional echo planar imaging (EPI)-based acquisitions (TR/TE 2000/30 ms, 90° flip angle, voxel size 3.5 × 3.5 × 3.5 mm) to measure BOLD contrast during the ERT and the VWMT, one functional EPI-based acquisition (TR/TE 2000/30 ms, 70° flip angle, voxel size 3.5 × 3.5 × 3.5 mm) sensitive to BOLD contrast during rest (RS), one T1-weighted structural scan for anatomical reference (TR/TE 9/3.5 ms, 8° flip angle, voxel size 1x1x1mm), and finally a pseudo-continuous arterial spin labelling (pCASL) acquisition (TR/TE 2000/14 ms, 90° flip angle, voxel size 3x3x3).

During the ERT, VWMT and RS acquisitions, simultaneous pupillometry will be recorded using an SR-Research MR-compatible Eyelink system (Mississauga, Canada). Besides changes in brain activation and pupil dilation, autonomic responses to emotional events and stimuli include increased skin conductance reactivity (SCR) and changes in cardiovascular activity (HRV) [107]. We will measure SCR during MRI scanning using an MR-compatible Direct Current Galvanic Skin Response MR sensor interfaced with the BrainAmp ExG MR amplifier (Brain Products, GmbH) by applying a constant voltage (.5 V) between two sintered Ag/AgCl electrodes attached to the palmar surface of the distal phalanges of the index and middle fingers of the left hand. Furthermore, HRV signal will be recorded during scanning, logging the R-top trigger produced by the standard cardiac equipment of the Philips and Siemens MRI systems. In order to correct for additional noise, respiratory rate and depth will be measured through pressure variation in a cushion that is fastened around the participant’s abdomen. Finally, before every fMRI acquisition, the state tension levels of the participant will be monitored, by asking them how tense they feel on a Visual Analogue Scale.

#### Randomization

Allocation sequence will be based on computer-generated random numbers. The first 50 rrMDD patients will be randomized over either the treatment condition or the waiting list control condition, to allow for instantaneous analysis of immediate PCT effects after inclusion of these participants. The 25 last included rrMDD patients will be allotted to the treatment condition, but will be given the same information (and thus hold the same expectations regarding their chance of being in the treatment condition). Patients and the principal investigators will not be blind to the treatment condition. However, to ensure unbiased assessment of clinical state and neuropsychological testing, the researchers who are involved in further assessments will be kept blind, and participants will be asked not to inform the assessor on their allotted condition.

### Statistical analyses

#### Questionnaire and behavioural data

Cross-sectional residual characteristics of remitted MDD will be tested with a (Repeated Measures-, in case of highly correlated task conditions) AN(C) OVA procedure. The effects of PCT as measured with questionnaires and cognitive tests before and after treatment will be analysed within a multi-level analysis framework. Appropriate nonparametric tests (e.g. Friedman test) will be used if warranted. Effects will be considered significant at *p* < .05. Age, sex, and education level will be added as covariates.

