#### Sample size

A total of 100 participants will be included, of which 75 rrMDD patients and 25 HCs. Power analyses for behavioural data, performed with G*Power 3.9.1.4, show that groups of 25 are sufficient to detect moderate effects (with 80% power and α = 0.05) for both cross-sectional group comparisons and longitudinal treatment effect analyses. Exact power analyses for fMRI analyses are difficult, due to the complex mass univariate nature of the data. However, previous comparable imaging studies yielded sufficient power with the inclusion of 20 participants per group [21, 37, 64, 70, 78, 82, 83]. We will include a minimum of 25 (carefully selected) participants per group, to allow for loss of data due to follow-up drop-outs.

The inclusion of 75 rrMDD patients allows for several lines of analysis. Firstly, cross-sectional comparisons will be carried out in 50 rrMDD patients versus 25 HCs in order to establish residual abnormalities in emotion processing. Because of an (unforeseen at the time of planning of the study) replacement of the MRI scanner, the last included 25 rrMDD patients (all allotted to the treatment condition) will be scanned on a different scanner, and will therefore not be included in this analysis. Secondly, longitudinal analyses of immediate treatment effects will be performed in the first 50 rrMDD patients who were randomized to either the therapy group or the waiting list control (25 vs. 25). Finally, since it is expected that 50% of rrMDD patients relapses within 1,5 years [41, 59], an additional group of 25 rrMDD patients will be included for the PCT condition, expanding the group of participants receiving treatment to *n* = 50 to allow analyses of pre-post differences in relation to clinical outcome at 18-month follow-up. Even though these last 25 patients will be scanned on a different MRI scanner, we will ensure that all participants have their pre- and post-treatment scanning session on the same MR machine.

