#### MRI data

Quality of BOLD fMRI data will be extensively checked, before data will be pre-processed according to standard recommended procedures. Subsequently, data will be modelled on the subject level using onsets/duration for the different task conditions, or time-course information. On the second level, between-group comparisons will be performed in order to analyse residual abnormalities in emotion regulation capacity, verbal working memory performance and resting state-perfusion and functional connectivity. A multilevel analysis model will be set up to test for the effects of treatment on these measures. Furthermore, linear modelling will be applied to identify and test the predictors of long-term treatment success, as defined by symptomatology (at T0, T1, T2) and relapse status and course (T1-T2) in the larger sample of remitted patients who have received therapy. Multivariate pattern analysis will be performed to evaluate the predictive value of post-treatment characteristics and pre-treatment changes for long-term treatment success. Effects will be considered significant at *p* < .05, corrected for multiple comparisons.

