#### Pupillometry data

Pupillometry data will be corrected for eye blinks and modelled to task data. Summary statistics will be entered in (Repeated Measures-)AN(C) OVAs, multi-level models and linear regression models. Effects will be considered significant at *p* < .05 after appropriate correction for multiple comparisons. To investigate whether PDR measurements have value for predicting frontal brain activation during emotion regulation, the PDR will be related to functional activation of regions implicated in effortful emotion regulation using multiple regression, while controlling for the arousal component of the sympathetic response, in the form of variation in SCR and HRV.

To investigate whether these relations are unique for effortful emotion regulation, linear regression models of the PDR during effortful emotion regulation (ERT) and during working memory (VWMT) will be set up and compared. Finally, it will be investigated whether treatment success can be predicted from multivariate patterns based on information from different modalities.

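### The plan does not say how T0 enters the randomised PCT v waiting-list model; an arm-by-time model with free baseline means would give up precision that T0 adjustment recovers

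*Protocol article*

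**What the plan says.** All references are to the protocol article.

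- **Questionnaire and behavioural data:** PCT effects on questionnaires and cognitive tests, taken at T0 and T1, "will be analysed within a multi-level analysis framework". The paragraph ends: "Age, sex, and education level will be added as covariates". It gives no fixed terms for arm, time or baseline.
- **Primary outcome measures:** for the mechanism aim, "Changes in these measures following PCT at T1 are the main study parameters in the assessment of the working mechanisms of PCT". The Aims section likewise describes a within-subject comparison before and after PCT, set against the waiting list.
- **MRI data:** "A multilevel analysis model will be set up to test for the effects of treatment on these measures". No covariates are named.
- **Pupillometry data:** "Summary statistics will be entered in (Repeated Measures-)AN(C) OVAs, multi-level models and linear regression models". No covariates are named here for the treatment effect.
- **Sample size and Randomization:** immediate treatment effects are tested in the first 50 patients, randomised 25 v 25. The last 25 patients are all allotted to PCT and are outside this comparison.
- **Discussion:** an estimated 20% loss is allowed for, and drop-outs are to be replaced where possible.

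**The concern.** With two time points, complete data and arm-specific T0 means, the arm-by-time term in a multilevel model is the difference between arms in mean change. In a randomised comparison the T0 means are equal in expectation. The model therefore spends information on estimating a baseline difference known to be zero apart from chance. Adjusting T1 for T0, or giving the two arms one T0 mean, uses that knowledge.

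The covariates that are named do not make up for this. When data are complete and variances equal, time-constant covariates entered as main effects cancel out of the arm-by-time contrast.

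This is the trial's only randomised comparison and the main test of its second aim, with 25 patients per arm before losses. The T0 values are already collected for these measures (Table 1), so any precision lost here is lost for no saving.

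**Working it through.** **The plan's own figure.** The article says that "groups of 25 are sufficient to detect moderate effects (with 80% power and α = 0.05") for both cross-sectional and longitudinal comparisons. This cannot be reproduced exactly, because it gives no numerical effect, no test and no ρ. Taking d = 0.5 and two-sided α = 0.05, a two-group comparison at 25 v 25 has 41% power. Taking a repeated-measures interaction of f = 0.25 with 50 patients in all, power is 83% at ρ = 0.3 and 93% at ρ = 0.5. So the statement can be met for the longitudinal comparison under the second convention. Whether the sample size is adequate is a separate matter; the figure does not reveal which model is planned.

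**Inputs for the check.** n = 25 per arm (Sample size); n = 20 after the 20% loss (Discussion). Assumed: ρ from 0.3 to 0.8, equal SDs (σ) at T0 and T1, a T1 difference of 0.5 SD, two-sided α = 0.05.

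**Formulas.** The variance of the estimated effect is (2/n)σ² times a factor:
- arm-by-time with free baselines (change score): 2(1−ρ)
- T0 as covariate: 1−ρ²
- ratio, adjusted to change score: (1−ρ²) / [2(1−ρ)] = (1+ρ)/2

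The direction does not depend on equal SDs. With SDs s0 and s1, the change-score variance exceeds the variance of T1 given T0 by (s0 − ρs1)², which is never negative. Only the ratio (1+ρ)/2 needs equal SDs.

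**Slope cost.** Estimating the T0 slope inflates the adjusted variance by about 1 + 1/(N−4). That is 1 + 1/46 = 1.022 at N = 50 and 1 + 1/36 = 1.028 at N = 40.

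| ρ | Change factor | Adjusted factor | Ratio | Ratio × 1.022 (N = 50) | Power, 25 per arm | Power, 20 per arm | Detectable at 80% power, 25 per arm (SD) |
|---|---|---|---|---|---|---|---|
| 0.3 | 1.40 | 0.91 | 0.65 | 0.66 | 31% → 44% | 26% → 37% | 0.96 → 0.77 |
| 0.5 | 1.00 | 0.75 | 0.75 | 0.77 | 41% → 52% | 34% → 43% | 0.81 → 0.70 |
| 0.7 | 0.60 | 0.51 | 0.85 | 0.87 | 61% → 68% | 51% → 58% | 0.63 → 0.58 |
| 0.8 | 0.40 | 0.36 | 0.90 | 0.92 | 78% → 82% | 68% → 73% | 0.51 → 0.49 |

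Arrows run from change score to T0-adjusted. Power and detectable differences come from the noncentral t without the slope cost, so the adjusted figures are slightly generous.

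**Simulation** (3000 trials, 25 per arm, complete data, no further covariates). The SD of the estimated effect for change score, T0 as covariate, and a mixed model with a common T0 mean was:
- ρ = 0.3: 0.331, 0.270, 0.270
- ρ = 0.5: 0.279, 0.248, 0.248
- ρ = 0.7: 0.211, 0.198, 0.198

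The last two agree, so the common-mean model recovers the full gain. At ρ = 0.3, (0.270/0.331)² = 0.665, in line with 0.66 in the table.

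**If the planned model already has a common T0 mean,** the ratio is 1 and nothing changes.

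**The case against.** A reader might infer that the plan ignores the baseline measurement, or that it excludes T0 adjustment. The document supports neither.

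- T0 is in the model already, as a repeated outcome. What is not stated is whether the arms share a T0 mean. A common-mean model fits the phrase "will be analysed within a multi-level analysis framework" just as well.
- Age, sex and education are named but are not said to be the only covariates. That sentence closes a paragraph which also covers the cross-sectional comparison, where T0 is the outcome and could not be a covariate. Its silence on T0 is weak evidence.
- Making change the main parameter does not fix the estimator. With T0 as a covariate, analysing change or T1 gives the same treatment effect.
- The text is thinner outside the questionnaires and cognitive tests. The MRI section names no covariates, and the pupillometry section lists AN(C)OVA among its methods.
- A journal article may leave exact model terms to the full protocol or analysis plan.
- Adjustment is not always better at this size. With the slope cost, break-even is at (1+ρ)/2 × 47/46 = 1, so ρ ≈ 0.96 at N = 50. With 37/36 it is ρ ≈ 0.95 at N = 40.
- The figures for 20 per arm make no allowance for replacing drop-outs.

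All of this stands, and it makes the point conditional. It does not remove it. The text that is given (before and after, change as the parameter, three covariates) reads most naturally as an arm-by-time model, and nothing in it supplies the adjustment. Either specification that recovers the precision fits within the planned framework.

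**Conclusion.** The point holds conditionally, as an improvement worth making. If the multilevel model has free baseline means, the randomised effect has about 2/(1+ρ) times the variance of a T0-adjusted estimate. The adjusted variance is then lower by 35%, 25%, 15% and 10% at ρ = 0.3, 0.5, 0.7 and 0.8, less 2–3% for the slope. Since ρ is not given and may differ between measures, no single figure can be claimed. The ratios assume equal SDs at T0 and T1.

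If the model already constrains the T0 means, the gain is zero. No bias or invalid test is involved: the unconstrained model is also an unbiased analysis of the randomised comparison. The case is firmest for questionnaire and cognitive outcomes and weaker for pupil and MRI outcomes.

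**What to change.** For the first 50 randomised patients, state in the analysis section that the treatment effect on questionnaire and behavioural outcomes, and on PDR or other scalar summaries, is the T1 difference between arms adjusted for the same measure at T0. Equivalently, specify a multilevel model with one T0 mean for the two randomised arms, which also keeps patients who have only a T0 value. Retain age, sex and education in either case.

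If the full plan already does this, one clause in the article saying so is enough.

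No new data are needed. For scalar outcomes the cost is one degree of freedom. Voxel-wise MRI needs more work: either a voxel-wise T0 covariate or a common-baseline specification.

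### The primary cognitive-bias measures are judged at p < .05 with no stated multiplicity correction, while the co-primary pupil measures, analysed in the same kinds of model, must survive one

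*Protocol article*

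**What the plan says.** Under Primary outcome measures the article states: "The primary outcome of the cross-sectional assessment of rrMDD characteristics is threefold". The three parts are cognitive biases, BOLD response and the pupil dilation response (PDR). The first part is described as "cognitive biases to negative and positive emotional information (measured with the Attentional Response to Distal vs. Proximal Emotional Information task (ARDPEI") together with "an adapted version of the Emotional Reasoning Task [87] and an Implicit Association Task (IAT"), so it has three tasks. The same section carries all three parts into the treatment aim: "Changes in these measures following PCT at T1 are the main study parameters in the assessment of the working mechanisms of PCT".

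The Statistical analyses section gives each type of data its own significance rule:

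- Questionnaire and behavioural data: "Effects will be considered significant at *p* < .05. Age, sex, and education level will be added as covariates".
- MRI data: "Effects will be considered significant at *p* < .05, corrected for multiple comparisons".
- Pupillometry data: "Effects will be considered significant at *p* < .05 after appropriate correction for multiple comparisons".

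No other part of the article adds a correction for the behavioural data. The Sample size section powers those data at a single alpha of 0.05.

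**The concern.** Two of the three parts of the primary outcome carry an explicit multiplicity rule and the third does not. The contrast with pupillometry is the telling one. Pupil summary statistics go into AN(C)OVAs, multilevel models and regressions; behavioural scores go into AN(C)OVAs and multilevel models. Table 1 shows that PDR is recorded during the ARDPEI and the IAT. So, for the same task and the same participants, the pupil result has to survive correction and the bias score does not.

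At stake is the error rate of the cognitive-bias claims, above all the first aim's claim of residual bias in remitted patients against controls. One nominal p below .05 on any of several bias scores would count as a primary finding, whereas a pupil result with the same p-value might not.

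**Working it through.** **Inputs from the article.** Three bias tasks, covering negative and positive information (Primary outcome measures); p < .05 per test (Questionnaire and behavioural data); 50 patients versus 25 controls cross-sectionally, 25 versus 25 longitudinally, 80% power and alpha 0.05 for moderate effects (Sample size); 20% loss (Discussion).

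**Assumptions not in the article.** Number of tests k per aim: 3 (one per task) or 6 (each task tested by valence). Correlation between test statistics: 0 to 0.7. Moderate effect: d = 0.5 or f = 0.25. Correlation between repeated measures: 0.5 unless stated. Tests are two-sided.

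**1. The plan's own power figure.** It cannot be reproduced uniquely, because the effect size is not given as a number and the test is not named. Candidate readings at alpha 0.05:

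- Two-sample t, d = 0.5, noncentrality d × √(n1·n2/(n1+n2)): 41% for 25 versus 25 and 52% for 50 versus 25.
- Group-by-time interaction in a repeated-measures model with two occasions, f = 0.25, N = 50, λ = N·2·f²/(1−ρ): 69% at ρ = 0, 83% at ρ = 0.3, 93% at ρ = 0.5.

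The error-rate argument below does not depend on which reading was meant.

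**2. Family-wise error within one aim at .05 per test.** For independent tests this is 1 − 0.95^k:

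- k = 3: 1 − 0.95³ = 0.143
- k = 6: 1 − 0.95⁶ = 0.265

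For equally correlated normal test statistics (simulation, 400,000 draws):

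| Correlation | k = 3 | k = 6 |
|---|---|---|
| 0 | 14.3% | 26.5% |
| 0.3 | 13.6% | 24.1% |
| 0.5 | 12.6% | 20.7% |
| 0.7 | 11.0% | 16.5% |

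Every cell is at least twice 5%.

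**3. What correction costs.** Holm compares the smallest p-value with 0.05/k, so its strictest step equals Bonferroni: 0.05/3 = 0.0167 or 0.05/6 = 0.0083. Later steps are looser, so these are worst-case costs.

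| | alpha 0.05 | 0.0167 (k = 3) | 0.0083 (k = 6) |
|---|---|---|---|
| d detectable with 80% power, 50 vs 25 | 0.70 | 0.81 | 0.87 |
| Power, 50 vs 25, d = 0.5 | 52% | 35% | 26% |
| Power, group × time, N = 50 (λ = 50·2·0.0625/0.5 = 12.5) | 93% | 85% | 78% |
| Power, group × time, N = 40 after 20% loss (λ = 10) | 87% | 74% | 65% |

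**The case against.** The behavioural paragraph never says that its tests are uncorrected. It is a short paragraph in a condensed article, and the grouping of tests is often left to an analysis plan. That limits the claim to a correction not being stated. But the threshold itself is not left open: a rule is given, and it differs from the rule in the two sections that follow.

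The MRI correction may be aimed mainly at voxel-wise testing, since the article calls those data mass univariate. This is fair, and the comparison should rest on pupillometry, where summary statistics are tested.

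Repeated-measures models may take valence into one model per task, so six tests cannot be assumed. This also stands, and is why the range starts at three. Such models do not combine the three tasks, and they can yield more than one effect per task.

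A reader might infer more than the article supports:

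- *All questionnaires are at fault.* The article calls them secondary and gives them a supporting role in interpretation. Depressive symptoms as an outcome of the long-term prediction models fall under the corrected rule in the MRI data section.
- *The error rate is 46%.* That figure (1 − 0.95¹²) pools baseline and change. These answer separate aims with separate hypotheses, so the family belongs within each aim.
- *A PCT mechanism could be claimed from behaviour alone.* The second aim's hypothesis concerns changes in prefrontal and limbic activation and connectivity that accompany normalised processing. A bias result on its own would not establish it.

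**Conclusion.** The point holds for the primary cognitive-bias tasks. A primary part of the outcome has a stated threshold with no stated correction, next to another primary part that is corrected in the same kinds of model. Within each aim the chance of at least one false-positive bias result is about two to three times the nominal 5% with one test per task, and about three to five times with testing by valence. These sizes rest on the assumed number of tests and on correlations between 0 and 0.7; the article fixes neither. The point does not extend to the secondary questionnaires as a defect, nor to error rates pooled across aims. It should be corrected before the bias results are presented as primary findings.

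**What to change.** In Questionnaire and behavioural data, state that effects on the primary cognitive-bias measures (ARDPEI, Emotional Reasoning Task, IAT) are judged after Holm correction across those tests within each aim, and list the tests that make up the family. Alternatively, name one primary bias measure, which avoids the loss of power for that measure but moves the other tasks to a secondary role. Describe the p-values of the secondary questionnaires as supportive or exploratory.

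No data collection changes. The price is the power loss shown in the working: in the six-test case, the cross-sectional comparison loses sensitivity and longitudinal power drops below 80% even before dropout, under the assumed f = 0.25 and ρ = 0.5. The alpha 0.05 power statement under Sample size should therefore be restated at the adjusted level, with the effect size and the test named.
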